#### Secondary outcomes

Secondary outcomes will include target lesion onset time, DLQI, TCM syndrome score, and the relapse interval of the target lesion.

### Data collection

Data will be collected using a CRF. The research medical records and case reports will be completed by the researcher for all enrolled patients. Completed case reports will be reviewed by the clinical monitor, and then handed over to the data administrator for data entry and management.

The following patient information will be collected: general information (including name, gender, birth date, marriage status, time of disease diagnosis and onset), complaint and symptoms, family history, use of pharmaceutical drugs, physical examination, skin lesions, additional symptoms evaluated using the TCM scale, target lesion imaging and scoring, and the DLQI questionnaire. Information regarding adverse events will be recorded during the procedure and on follow-up. Images of skin lesions, PASI scores, TCM syndrome assessment, DLQI, etc. will be performed at patient enrollment and after 2, 4, 6 and 8 weeks of treatment and during the follow-up period (12 and 24 weeks after intervention is completed).

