### Interventions

#### Fire needling

In Group A1, patients will be treated with fire needling. Filiform needles will be used prior to fire needles. This is based on the treatment principles of WeiTong as well as “promoting blood circulation” and “removing blood stasis” using the He’s SanTong method from the Beijing Hospital of Traditional Chinese Medicine.

Fire needling will be conducted in a clinic of the Dermatology Department. The manipulation will mainly be operated on the target lesions. As the target lesions are mostly on the back and limbs of the body, participants will take a prone or sitting position.

The acupoints used for all participants in the intervention group are shown in Fig. 2. Positioning of the body acupoints will be based on the Chinese–English bilingual innovation textbook of the National College of Advanced Chinese Medicine in the new century “Meridians and Acupoints (Chinese-English)” [31]. The following acupoints (with their locations [32]) will be used:

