#### Moxibustion

In Group A2, patients will be treated with moxibustion. The acupoints used for all participants in the intervention group are shown in Fig. 2. This is also based on the treatment principles of WenTong, using the He’s SanTong method from the Beijing Hospital of Traditional Chinese Medicine.

This process will be carried out in a clinic of the Dermatology Department, separately from Group A1. The main region of moxibustion will be selected around the target lesion and the six acupoints. Participants will take a prone or sitting position

The selection principles will be similar to Group A1. The similar acupoints will be ST36 (Zusanli), SP10 and BL24 (Qihai). In addition, the acupoints will be positioned similarly to the previous reference group [24] and Group A1. Acupoints (with their locations [31]) will be positioned as follows:

ST36: On the anterior aspect of the leg, on the line connecting ST35 (Dubi, on the anterior aspect of the knee, in the depression lateral to the patellar ligament) with ST41 (Jiexi, on the anterior aspect of the ankle, in the depression at the center of the front surface of the ankle joint, between the tendons of extensor halluces longus and extensor digitorum longus), 3 B-cun inferior to ST35. ST36 is located on the tibialis anterior muscle.

SP10: On the anteromedial aspect of the thigh, on the bulge of the vastus medialis muscle, 2 B-cun superior to the medial end of the base of the patella.

BL24: In the lumbar region, at the same level as the inferior border of the spinous process of the third lumbar vertebra, 1.5 B-cun lateral to the posterior median line.

The target lesion and all matching acupoints will be treated with moxibustion simultaneously. The baixiao moxibustion device will be put on the target lesion and matched acupoints, with the installed moxibustion column. The moxibustion device is lit and the tube body is rotated to adjust the size of the gas vent to moderate the temperature (generally 42 °C). Each moxibustion column can be applied for 30 min. When the warm feeling disappears and the moxibustion tube is cool, indicating that burning is finished, the device can be removed. After moxibustion, artemisia oil will be used to massage the area for absorption.

Participants with a warm feeling will be seen to achieve the treatment response with moxibustion.

Moxibustion on the target lesion will be performed for 30 min each time, with the matching acupoints treated for 15 min each time.

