A baixiao moxibustion device will be used for patient treatment (Chongqing Baixiao Medical Equipment Co. Ltd.), which is composed of the moxibustion cover, positioning paper, moxibustion column, medical adhesive, moxibustion tube and so forth.

Treatment frequency and course will be three times a week for 8 consecutive weeks.

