### Control group

Patients in Group B will be treated with calcipotriol ointment. Calcipotriol ointment will be purchased from Leo pharmaceutical Co. Ltd., Ireland (15 g per bottle). Patients will be required to return the used tube for recycling and verification after every visit.

Treatment of the target lesion will be similar to the intervention groups. For each skin lesion (an area the size of the palm), a half-fingertip unit [33] of calcipotriol ointment will be administered. A fingertip unit refers to the dosage of a topical drug that is squeezed from a standard packaging hose with a diameter of 5 mm to an adult fingertip. Calcipotriol ointment will be applied based on the actual lesion area. Treatment frequency and course of intervention for the control group will be once every morning and evening for 8 consecutive weeks.

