### Criteria for discontinuing or modifying allocated interventions

The physician will manage the intervention and any related harm for all enrolled patients. Any suspected adverse events related to the treatment will be discussed with the Principal Investigator of the project team. Both the Principal Investigator and physician will be notified of all adverse events and the research team will conduct a quarterly review of all adverse events that may occur during the trial.

Adverse events may occur during the study. Patients who receive fire needling treatment may suffer from fainting, bleeding, body heat, dizziness and so on. Correspondingly, moxibustion treatment may cause scalding injury, allergy, dyspnea, asthma, etc. Topical drugs may cause local redness, irritation, burning, etc. We will establish detailed medical records of the above possible adverse reactions or suspected adverse events and have the necessary treatment measures in place to deal with these adverse events.

If the patient shows any discomfort, changes in their condition, or has any unexpected adverse effects, whether related to the treatments or not, the patient will be instructed to inform the physician. The physician will provide the necessary medical treatment to alleviate any adverse conditions. The physician will determine whether the study treatment is ineffective due to poor effects or for other medical reasons. Patients will be informed of the risks of intervention and possible reasons for adverse effects. The patient may make an appointment with the physician to consider discontinuing or modifying their interventions.

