We hypothesize that acupuncture and moxibustion could improve the effective treatment rate for plaque psoriasis and reduce the recurrence rate and related adverse events. Because of the high incidence and recurrence of psoriasis, current treatment strategies are not ideal. We believe that the results of this study will have important clinical significance, even if our study demonstrates that acupuncture and moxibustion have no clinical efficacy. This will demonstrate that more clinical studies are needed to find a safe and effective treatment strategy for plaque psoriasis. Finding an effective treatment for short- and long-term efficacy is key for psoriasis treatment. This will promote and popularize TCM for psoriasis treatment and other dermatological ailments. This is one of the main benefits of performing the current study.

Several limitations to our research design and study should be noted. First, because of the particularity of the fire needle procedure the method was difficult to blind. The moxibustion method has a risk of scalding and other adverse events. Second, patients visiting TCM hospitals may be inclined to choose TCM methods over Western medicine treatment, i.e., a reluctance to use calcipotriol ointment. This may lead to a lower enrollment rate and longer time to recruit patients for the control group. Third, because of fear of the fire needle procedure, patients may be reluctant to comply with the procedure or volunteer to be enrolled in the experimental group. Finally, the sample cohort was not large, with only patients in Beijing being selected for the study.

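### Adverse events will be ascertained more closely in the fire needling and moxibustion arms than in the calcipotriol arm, which weakens any between-arm reading of safety

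*Protocol article*

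**What the plan says.** All references are to the protocol article.

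- **Recording rule (Data collection).** "Information regarding adverse events will be recorded during the procedure and on follow-up". The word *procedure* is not defined. The same section schedules images, PASI, TCM syndrome and DLQI for every arm at enrolment, at weeks 2, 4, 6 and 8, and at 12 and 24 weeks after treatment. Adverse events are not named in that list.
- **Group A1 (Fire needling).** "Fire needling will be conducted in a clinic of the Dermatology Department", three times weekly for 8 weeks.
- **Group A2 (Moxibustion).** "This process will be carried out in a clinic of the Dermatology Department, separately from Group A1", and "Treatment frequency and course will be three times a week for 8 consecutive weeks".
- **Group B (Control group).** Ointment is applied "once every morning and evening for 8 consecutive weeks". Contact with staff is by visit: "Patients will be required to return the used tube for recycling and verification after every visit". Application at home is implied, not stated.
- **Reporting by patients (Criteria for discontinuing or modifying allocated interventions).** Patients in every arm are to tell the physician about discomfort or unexpected effects, related to treatment or not. The section also gives examples of expected harms by treatment; for Group B, "Topical drugs may cause local redness, irritation, burning, etc".
- **Use of the data.** The Discussion expects acupuncture and moxibustion to "reduce the recurrence rate and related adverse events". The Abstract says adverse events serve the safety assessment. They are not a listed primary or secondary outcome, and the Statistical analysis section names no test for them.
- **Blinding.** Only the statisticians are blinded.

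**The concern.** A comparison of adverse-event rates is fair only if events have a similar chance of being noticed in each arm. Here that chance depends on the treatment. A patient having needling or moxibustion is in front of a clinician every two to three days. A patient on ointment is scheduled to be seen once a fortnight. A brief local reaction is likely to be present at some session in A1 or A2, but can come and go between visits in B. The recording rule strengthens this imbalance, because it ties recording to a procedure without saying what that is for patients who use ointment.

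At stake is the safety half of the hypothesis in the Discussion. If mild, transient calcipotriol irritation is under-recorded, a true advantage of acupuncture or moxibustion could be hidden, or a disadvantage could appear where none exists. Those who record events know the allocation, so blinding does not protect the comparison.

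**Working it through.** The article states no adverse-event figure, so there is none to reproduce. The check counts contacts and then asks how far the imbalance could distort observed rates.

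**Step 1: contacts during treatment.**
- A1 and A2: 3 sessions per week × 8 weeks = 24.
- B: assessments at weeks 2, 4, 6 and 8 = 4.
- Ratio 24 : 4 = 6 : 1, taking the assessments in A1 and A2 to fall on session days.
- Mean interval between contacts: 7/3 ≈ 2.33 days in A1 and A2; 14 days in B.

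**Step 2: probability that an event is recorded.** Assumptions, none of them from the article: a single event lasting *d* days; the same true incidence in all arms; evenly spaced contacts; an event present at a contact is always recorded; and any event may also reach the record through the patient, by spontaneous report or later recall, with probability *q*, equal in all arms.

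- Seen at a contact: s = min(1, d / interval)
- Recorded: P = q + (1 − q) × s
- Apparent rate ratio, A1 or A2 versus B: P(A) / P(B)

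**Step 3: a 3-day event.**
- s(A) = min(1, 3/2.33) = 1; s(B) = 3/14 = 0.214
- q = 0: 1 / 0.214 = 4.67
- q = 0.5: 1 / (0.5 + 0.5 × 0.214) = 1 / 0.607 = 1.65
- q = 0.8: 1 / (0.8 + 0.2 × 0.214) = 1 / 0.843 = 1.19
- q = 1: 1.0

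**Step 4: other durations.**

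| Duration (days) | q = 0 | q = 0.5 | q = 0.8 | q = 1 |
|---|---|---|---|---|
| 1 | 6.0 | 1.33 | 1.09 | 1.0 |
| 2 | 6.0 | 1.63 | 1.17 | 1.0 |
| 3 | 4.67 | 1.65 | 1.19 | 1.0 |
| 7 | 2.0 | 1.33 | 1.11 | 1.0 |
| 14 | 1.0 | 1.0 | 1.0 | 1.0 |

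**Step 5: the same in patients.** Suppose, as a further assumption, that 20% of patients in every arm truly have one 3-day event. In an arm of 40 (the planned size of A2 and of B) that is 8 patients. A2 would record all 8. B would record 8 × 0.214 = 1.7 with q = 0, 8 × 0.607 = 4.9 with q = 0.5, and 8 × 0.843 = 6.7 with q = 0.8.

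The distortion is zero only if reporting is complete or events last as long as the interval between visits in B. Throughout the model it under-counts B.

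**The case against.** Several stronger readings are tempting, and the documents do not support them.

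- **A reader might infer that adverse events are never recorded in Group B during treatment.** That requires *procedure* to mean a needling or moxibustion session. The article does use the word for needling, but Fig. 1 is a flowchart of the trial procedure, and the pairing with follow-up matches the trial's two phases. Group B also has four assessments, and its expected reactions are among those for which medical records are promised. The imbalance is 24 to 4, not 24 to none.
- **A reader might infer that a planned statistical comparison is compromised.** None is named. What exists is a hypothesis in the Discussion and a safety assessment.
- **A reader might take the lists of expected harms as different prompts for each arm.** They are open-ended examples in a section on discontinuation. The calcipotriol list does not repeat the itching, dry skin and rash mentioned in the Background, but it does not exclude them.
- **A reader might take 6 : 1, or a ratio of 4.7, as the likely bias.** Both ignore patients' own reports, which the article asks for. Irritation that recurs with repeated application would also be caught more often than a single event.

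Two further objections carry weight. Part of the extra contact belongs to the interventions: fainting or scalding arises at sessions and should be recorded there. And Table 1, the visit schedule, is not shown, so common adverse-event collection at each visit cannot be ruled out; the wording of the questions is something an article may leave to the full protocol or case report form.

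What remains does not rest on omission. The article states a recording rule tied to an undefined term and a comparative hypothesis, and on either reading of the term the arms are observed with unequal intensity.

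**Conclusion.** The concern holds as differential ascertainment of adverse events. The contact imbalance of 24 to 4 follows directly from the schedules. It makes short-lived mild events more likely to be recorded in A1 and A2 than in B, and so weakens any between-arm reading of adverse events, including the expectation of fewer related events with acupuncture and moxibustion.

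The size is unknown. On the assumptions above, the apparent ratio for a 3-day event runs from about 4.7 with no spontaneous reporting to 1.0 with full reporting, with about 1.65 and 1.2 at 50% and 80%. Because the article asks patients to report problems, the lower part of that range is more credible than the top, but an instruction to patients does not secure complete reporting.

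The bias probably runs against the trial's own hypothesis. A reader might infer that the safety conclusion could be wrong in either direction; the contact imbalance alone does not show that, although unblinded recording means the net direction cannot be guaranteed. The efficacy outcomes are not touched. This is a cheap improvement, not a flaw that undermines the trial.

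**What to change.** In Data collection, replace the sentence on adverse events with a rule that does not depend on treatment arm:

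- Adverse events are elicited in all three arms with the same questions: one common checklist, pooling the events named in the Background and in the section on discontinuing or modifying interventions, plus one open question.
- This is done at the existing assessments (weeks 2, 4, 6 and 8, and 12 and 24 weeks after treatment), each covering the period since the last assessment.
- Any between-arm comparison of adverse events uses these elicited reports only.
- Events observed at needling or moxibustion sessions are recorded as they occur and reported separately, as procedural safety data.

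Because follow-up ends at relapse (Study retention), show the number of patients still followed beside the two follow-up assessments.

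The cost is one common case report form page at visits already scheduled and one sentence on analysis. No extra visit is needed, and the sample size is unchanged. The small downside is that mild events seen only at a session and not recalled at the next assessment leave the comparative table; they still appear in the procedural safety report.

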### Patient dropouts

Investigators will have the authority to terminate patient participation at any time if the investigator deems it is in the best interests of the patient. Furthermore, the patient will have the right to withdraw consent to participate in the study at any time for any reason without any consequences for further medical treatment. Patient study discontinuation will be documented.

Termination criteria are as follows: 1) patients with serious adverse event based on the investigator’s judgment will terminate patient study participation; 2) the patient’s condition is aggravated during the course of the disease, and serious complications or rapid deterioration of the condition result in patient treatment discontinuation; 3) other adverse symptoms affecting the study observation or patient wellbeing; 4) unrelated medical reasons; 5) deviations in the clinical trial protocol, such as poor compliance or difficulty in evaluating drug effects; 6) patient thinks there is a lack of effect and voluntarily withdraws; 7) the patient is unwilling to continue clinical treatment during the clinical trial protocol; and 8) patients are administered glucocorticoids and/or immunosuppressive drugs, calcineurin inhibitors, retinoids, and vitamin D3 derivative preparations during the study.

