### Study outcomes

#### Primary outcomes

The primary outcomes will include the relapse rate and PASI score of the target lesions [34, 35]. The relapse rate will be defined as the recurrence of skin lesions after recovery that reaches 50% of the original PASI score, based on the American Academy of Dermatology Expert Association.

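### Termination criteria 5, 7 and 8 may take patients who depart from treatment out of the study, so the promised intention-to-treat analysis may lack their later PASI and pre-relapse follow-up

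*Protocol article*

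**What the plan says.** The Patient dropouts section first lets investigators end a patient's participation when they judge that to be in the patient's interest, and lets patients withdraw consent. It adds: "Patient study discontinuation will be documented". Eight termination criteria follow. Three of them describe departures from treatment:

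- Criterion 5: "deviations in the clinical trial protocol, such as poor compliance or difficulty in evaluating drug effects".
- Criterion 7: "the patient is unwilling to continue clinical treatment during the clinical trial protocol".
- Criterion 8: "patients are administered glucocorticoids and/or immunosuppressive drugs, calcineurin inhibitors, retinoids, and vitamin D3 derivative preparations during the study".

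The list is not uniform. Criterion 1 (serious adverse events) ends participation in the study. Criterion 2 says that "serious complications or rapid deterioration of the condition result in patient treatment discontinuation". Criteria 5, 7 and 8 do not say whether treatment or study participation ends.

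Under Data collection, PASI is scored at enrolment and "after 2, 4, 6 and 8 weeks of treatment and during the follow-up period (12 and 24 weeks after intervention is completed". Under Primary outcomes, the two primary outcomes are relapse and target-lesion PASI, and "The relapse rate will be defined as the recurrence of skin lesions after recovery that reaches 50% of the original PASI score". The Statistical analysis section promises both per-protocol and intention-to-treat analysis of the main efficacy measures, with survival analysis for relapse.

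**The concern.** Poor compliance, stopping treatment and taking another drug all happen after randomisation, and none is a refusal to be followed up. These are the patients in whom an intention-to-treat analysis differs from a per-protocol one, so the former needs their outcomes. If assessment stops when a criterion is met, their later PASI is missing and their time to relapse is censored at that point.

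The censoring may be informative. Patients, researchers and the outcome evaluators involved in treatment are unblinded (Blinding section), and criterion 5 includes a judgement about how well the effect can be evaluated. Under criterion 8, a patient who is worsening and starts a steroid before reaching the relapse threshold would be censored shortly before a likely relapse. That mechanism is inferred from the text, not stated in it. Loss may also differ by arm: the Discussion expects, because of fear of fire needling, that "patients may be reluctant to comply with the procedure or volunteer to be enrolled in the experimental group". Its remark on calcipotriol concerns recruitment, not compliance.

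An analysis plan can choose a method for missing data, but it cannot restore outcomes that were never collected.

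**Working it through.** **1. Does any section keep these patients under assessment?**

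- Data collection: case reports are completed for all enrolled patients, but there is no rule for visits after termination.
- Relevant concomitant care: glucocorticoid or immunosuppressant use is recorded on the CRF. Continued assessment is not mentioned.
- Study retention: follow-up begins after 8 weeks of treatment and ends at relapse. It gives no route into follow-up for someone who stopped early.
- Data collection again: the late visits are timed from completion of the intervention, which is undefined for a patient who does not complete it.

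None of these sections retains the patient.

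**2. What one termination costs.** Scheduled PASI assessments: 1 (enrolment) + 4 (weeks 2, 4, 6, 8) + 2 (12 and 24 weeks after treatment) = 7.

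| Terminated | Assessments lost |
|---|---|
| after week 6, before week 8 | 3 of 7 (week 8 and both follow-up visits) |
| after week 4, before week 6 | 4 of 7 |
| after week 2, before week 4 | 5 of 7 |

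Each row includes the 12-week visit, the time point of the relapse rates used for sample size. Relapse counts only after recovery. Termination before recovery therefore also loses the knowledge of whether recovery occurred, while termination after recovery loses time at risk.

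**3. Scale, as illustration only.** The plan gives no termination rate. Its related figures are relapse of 38% (A1) and 67% (B), 66 and 33 evaluable patients, and 80 and 40 randomised. Recomputing with a two-sided pooled Z test, alpha 0.05, power 0.80 and 2:1 allocation gives 68 and 34, and power 0.789 at 66 and 33, close to what is stated.

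Let dA and dB be the fractions with unknown relapse status, and xA and xB (each between 0 and 1) their unknown relapse proportions. The all-randomised difference B minus A1 is

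D = (1 − dB) × 0.67 + dB × xB − (1 − dA) × 0.38 − dA × xA,

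and its possible range has width dA + dB. One patient adds 1/80 = 1.25 points in A1 or 1/40 = 2.5 points in B. With loss in A1 only (dB = 0) and observed rates as planned (29 points):

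- 4 of 80 (assumed): 0.67 − 0.95 × 0.38 − 0.05 × xA = 0.309 − 0.05 × xA, so 25.9 to 30.9 points.
- 8 of 80 (assumed): 0.67 − 0.90 × 0.38 − 0.10 × xA = 0.328 − 0.10 × xA, so 22.8 to 32.8 points.

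These are logical limits, not expected bias. They take all randomised patients as denominator and treat relapse as yes or no. The protocol counts relapse only after recovery, at an unstated rate, and plans survival analysis, which uses time observed before censoring.

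**The case against.** The strongest reply is that the text can be read the other way. Criterion 2 speaks of stopping treatment, criterion 7 of unwillingness to continue treatment, and the opening authority is discretionary and tied to the patient's interest, so it need not govern poor compliance. Recording steroid use on the CRF, monitoring medication during follow-up and promising two analysis sets all fit better with patients who stay in. The article is also condensed, and protocol version 2.0 is not shown, so a rule for off-treatment follow-up may exist there.

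Much of this stands as a limit on certainty. A reader might infer that the protocol definitely removes these patients and that the intention-to-treat analysis is bound to lack their data. The mixed wording does not support that. But the article gives the criteria in full, in a section on leaving the study, so the problem lies in what is stated and not only in silence. Three hospitals could apply an ambiguous rule differently.

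A reader might also infer a bias in favour of fire needling, or take the whole loss allowance (80 − 66 = 14 in A1 and 40 − 33 = 7 in B) as the size of the problem. Neither is supported. The documents give no direction, and the allowance covers loss from any cause.

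For criterion 8, following patients through rescue medication is not the only defensible choice, because their outcomes then partly reflect the rescue drug. That is a fair point about what is being estimated. It does not apply to criteria 5 and 7.

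**Conclusion.** The point holds as a risk created by the protocol's wording. On the more natural reading, patients meeting criteria 5, 7 or 8 leave the study, no section keeps them in the scheduled assessments, and the intention-to-treat analysis may lack their later PASI and pre-relapse follow-up. The firm figure is per patient: at least 3 of 7 PASI assessments, including both follow-up visits, for anyone terminated before week 8. How often this would happen, and the size and direction of any bias, are unknown; the 4 and 8 of 80 are assumptions. Confidence is medium because the treatment-only reading remains possible. The wording should be changed, since both primary outcomes are affected and the remedy is cheap.

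**What to change.** - State that criteria 5, 7 and 8 stop study treatment only.
- For every randomised patient who does not withdraw consent to follow-up, continue the scheduled assessments and the existing app or telephone monitoring until relapse or the 24-week visit. Time the visits from scheduled week 8, the planned end of treatment, so that an early stop does not move them.
- Analyse these patients in their randomised arm.
- Limit criterion 8 to non-study use of the listed drugs, recorded on the CRF. As worded, its mention of vitamin D3 derivatives does not exempt the calcipotriol allocated to Group B, which is a slip of wording.

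The cost is protocol and CRF wording and a few already planned visits for patients off treatment. Outcomes after rescue drugs will partly reflect those drugs, so their use must be recorded. The change recovers neither PASI after relapse, because follow-up ends there, nor the outcomes of patients who refuse follow-up.
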